##### Healthy controls

Before the beginning of the whole clinical trial, the immediate alpha, beta, delta, and theta bands of the eyes-closed resting state EEG of the healthy controls in a quiet, without any interference laboratory will be recorded and ask them to do the “reaching and retrieving” gross movement, recording the real-time sEMG parameters (RMS and MF) of BB, TB, ECR, B, ED, and FCU during the whole process of the motion. The computer software calculates iEMG and MPF values.

#### Secondary outcome measures

Before and after the whole trial, the secondary outcome variables including MBI (a daily functional activity assessment) [22], CSS (a neurological deficits assessment) [23], FMA-U (a motor function assessment for upper limb) [24], MMT (a muscle strength assessment), and Brunnstrom (a limb function
recovery assessment) [25] are evaluated.

##### Sample size estimation

Sample size estimation was carried out according to the study objectives and protocol, and the difference between RMS values of sEMG of BB was obtained from the pretest of group 1 and group 2 after treatment and the healthy group. The difference between the healthy group and group 1 was 167.61 and 68.17 for group 2, and the standard deviations were respectively 127.22 and 148.46. The study effect size is 0.8, *α* = 0.05, test efficiency 1 − *β* = 0.80, and the number of sample groups is two. The sample size of each group is 25, and the total sample size is 50. Considering the possibility of sample loss in the trial, the sample size should be increased by 20%. Finally, the total sample size of this study should be 60 and divided into two groups with 30 sample size for each group.

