##### Data statistical analysis

The SPSS 26.0 statistical software will be used for analysis by three-party statisticians. Data presentation: each measurement is presented as mean ± standard deviation if it conforms to a normal distribution, or median and quartiles if it does not. Intra-group comparisons: if the measurement data in each group conforms to a normal distribution, paired *T* test will be used for comparison between each group before and after treatment; if all data does not conform to a normal distribution, paired sample Wilcoxon rank sum test is used. Inter-group comparison: If the measurement data of conforms to a normal distribution, one-way ANOVA will be performed, and the LSD method will be used for comparison between the groups (Welch’s test will be used to correct Dunnett’s T3 method when the variance is not equal); if the data does not all conform to a normal distribution, non-parametric test will be performed (Mann–Whitney *U* method is applied for comparison between two groups, and Kruskal–Wallis *H* method is for comparison between multiple groups).

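### The stated effect size of 0.8 does not follow from the pilot figures beside it, which give 0.72; two-sided power for the pilot difference is about 70% at the planned 25 evaluable per arm, not 80%

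*Protocol article*

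**What the plan says.** The protocol article, under Sample size estimation, sizes the trial on the RMS value of the biceps brachii sEMG after treatment, using a pretest. It reports: "The difference between the healthy group and group 1 was 167.61 and 68.17 for group 2, and the standard deviations were respectively 127.22 and 148.46". Planning inputs follow in the next sentence: "The study effect size is 0.8", alpha 0.05, and "test efficiency 1 − *β* = 0.80", for two groups. The result is "The sample size of each group is 25, and the total sample size is 50". The allowance for loss reads "Considering the possibility of sample loss in the trial, the sample size should be increased by 20" per cent, which brings the total to 60, or 30 per arm.

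The paragraph does not say how 0.8 was obtained, whether the test is one- or two-sided, or what loss rate is expected. Under Data statistical analysis the planned between-group comparison for normally distributed data is given as "one-way ANOVA will be performed, and the LSD method will be used for comparison between the groups", with rank tests otherwise. No direction is given for any of these tests.

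**The concern.** The paragraph offers the pretest as the basis of the calculation and names no other source for 0.8, so a reader will take 0.8 as the standardised pilot difference. If the printed means and SDs give a smaller value, 25 per arm has less than the stated power to detect the difference the pilot showed. This paragraph is the only justification given for the trial's size. A null result would then be read as if the trial had had an 80% chance of detecting the pilot difference, when the chance of missing it would be nearer 30% than 20%.

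**Working it through.** **Inputs.** From Sample size estimation: differences from the healthy group 167.61 (group 1) and 68.17 (group 2); SDs 127.22 and 148.46; effect size 0.8; alpha 0.05; power 0.80; 25 per arm, then 30. Assumptions: the two SDs belong to groups 1 and 2 in that order; the pilot groups are weighted equally, since their sizes are not given; the test is two-sided.

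**1. The plan's own figure.** With the normal approximation, n per arm = 2(1.960 + 0.842)² / 0.8² = 24.5, which rounds up to 25. Then 50 × 1.2 = 60. Both figures reproduce from an effect size of 0.8 and a two-sided test.

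**2. Effect size from the pilot.**
- Between-arm difference: 167.61 − 68.17 = 99.44.
- Pooled SD: √[(127.22² + 148.46²)/2] = √[(16184.93 + 22040.37)/2] = √19112.65 = 138.25.
- Standardised difference: 99.44/138.25 = 0.719.
- Limits: 99.44/127.22 = 0.782 with the smaller SD alone; 99.44/148.46 = 0.670 with the larger.

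Any weighting of the two SDs falls between 0.670 and 0.782, so the unknown pilot group sizes cannot bring the value to 0.8.

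**3. Power for the pilot difference.** Two-sided t-test at 0.05, noncentrality = d × √(n/2), df = 2n − 2. At n = 25 and d = 0.719 the noncentrality is 2.543 and the critical value 2.011.

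| Analysed per arm | d = 0.719 | d = 0.782 | d = 0.8 |
|---|---|---|---|
| 24 | 68.4% | 75.5% | 77.4% |
| 25 | 70.3% | 77.3% | 79.1% |
| 30 | 78.2% | 84.5% | 86.1% |
| 32 | 80.8% | 86.8% | 88.3% |

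At d = 0.719, 32 per arm is the smallest size reaching 80% (31 by the normal approximation). A simulation with the two unequal SDs and Welch's test gives 68.4%, 70.3% and 78.1% at 24, 25 and 30 per arm, so unequal variances do not change the picture.

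**4. Difference detectable with 80% power** (SD 138.25): 0.81 SD, about 112 units, at 25 per arm; 0.74 SD, about 102 units, at 30 per arm. Both exceed the pilot's 99.44.

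**5. Could a one-sided test explain the figures?** At d = 0.719 a one-sided 0.05 t-test does need 25 per arm (80.6% power). But the paragraph states 0.8, and one-sided at 0.8 the requirement is only 20 (normal approximation) or 21 (t-test) per arm. The printed combination of 0.8, 0.05, 0.80 and 25 fits only a two-sided calculation.

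**6. Loss.** Falling from 60 to 50 is a loss of 10/60 = 16.7%. A 20% loss from 60 leaves 48, or 24 per arm. Going from 25 to 24 per arm costs about 2 percentage points of power (70.3% to 68.4%).

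**The case against.** The best defence is that power is defined at a stated effect. At 0.8, 25 per arm gives 79% to 81% (t-test or normal approximation) and 30 gives 86%, so the power statement is not false on its own terms. The protocol also never says that 0.8 was computed with a pooled SD, and dividing by 127.22 gives 0.78, which rounds to 0.8. The first part stands: the fault lies in the link from the pilot to 0.8, not in the step from 0.8 to 25. The second part does not repair that link. No reason is given for using the smaller SD alone, and 0.782 would itself need 26 (normal approximation) or 27 (t-test) per arm.

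It is also fair to say that 24 or 25 analysed per arm is not certain. The sEMG outcome is scheduled only to the end of three weeks' treatment, in inpatients, so later follow-up losses do not touch it. With all 30 analysed, power is 78%. That stands, and is why the power is given here as a range. On the other side, the section on the healthy control group says that data of withdrawn participants will not be used, and multiple imputation appears only as a sensitivity analysis, so losses would reduce the main analysis.

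Three stronger readings are tempting and are not supported:
- A reader might infer that the 20% loss allowance is misapplied. The text says to increase the size by 20%, and 50 × 1.2 = 60 does that. It would be an error only if 20% were the expected loss rate, which is not stated.
- A reader might count 25 instead of 26 per arm at 0.8 as a mistake. It is the normal approximation against the t-test, one patient per arm.
- A reader might say flatly that the trial has 68% to 70% power. That holds only for a two-sided test, at the pooled pilot effect, with 24 or 25 analysed per arm.

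**Conclusion.** The point holds. The stated effect size of 0.8 is not what the adjacent pilot figures give: they give 0.72 with the pooled SD and cannot exceed 0.78. For the pilot difference of 99.44, power is about 70% at the 25 evaluable per arm that the protocol plans for, 68% at 24 and 78% if all 30 per arm are analysed; 80% needs 32. The effect size accounts for most of the shortfall: at 25 per arm it alone moves power from 79% to 70%.

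The effect-size mismatch needs no assumption beyond reading the two SDs as those of the two groups. The power figures also assume a two-sided 0.05 test, which is not stated but agrees with the planned non-directional tests and is the only reading under which 0.8 yields 25.

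**What to change.** Rewrite the sample size paragraph so that it:
- gives the effect size as 99.44/138.25 = 0.72 and shows the derivation, or, if 0.8 was chosen on other grounds, states those grounds and reports the pilot value beside it;
- states whether the test is one- or two-sided;
- reports two-sided power for the pilot difference as about 68% to 78% over 24 to 30 analysed per arm;
- gives the difference detectable at 80% power: about 0.81 SD (112 units) at 25 per arm and 0.74 SD (102 units) at 30 per arm;
- as a minor clarification, says that 60 randomised tolerates a loss of 10/60 = 16.7% before falling below 25 per arm.

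Do not enrol more. Baseline sEMG is already scheduled, so adjusting for it could recover some power, but the documents give no baseline correlation r and any gain should be shown as a range. Replacing d by d/√(1 − r²), power at 24 to 25 per arm would be about 72% to 74% if r = 0.3 and 80% to 82% if r = 0.5; both correlations are assumptions.

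The cost is one reworded paragraph and a less favourable stated power. No patients, visits or measurements are added.

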##### Management and safety monitoring

Before the initiation of this trial, the feasibility and innovation of this protocol have been discussed comprehensively in the seminar composed of five authoritative experts in the field. Then, the task will be divided, and the relevant personnel should receive training. To prevent treatment bias, all the staff including doctors, physiotherapists, group allocation workers, data collectors, data registers, and data processing analysts need to be trained in advance on the tasks they are responsible for. Participants are all anonymous in this trial, and their demographic information will be stored in a Word file with a password kept by the manager, and their trial data will be recorded in another Word file by relevant staff without any participants’ information. If there is any special circumstance, all trial personnel should be informed in advance, and approval should be obtained before checking the participants’ relevant records. The project manager, researchers, and experts from the Ethics Committee of the Second Affiliated Hospital of Heilongjiang University of Chinese Medicine are mainly responsible for the quality control of these trials.

In order to achieve the ability of standard operation procedure (SOP), filling in of case report form (CRF), Electronic Data Capture (EDC) system, and data entry. All data will be accurately double-entered into the EDC system, and the electronic CRF will be identical to the paper CRF. Moreover, multiple imputation will be used to deal with the missing data as part of the sensitivity analysis.

##### Trial conduct auditing

In order to timely discover and solve the problems encountered in the study duration, the Project Management Group will check the trial records and hold a group meeting to review trial conduct twice a week. Meanwhile, the Trial Steering Group (including acupuncture and rehabilitation physicians, instrument engineer, and data analysts) and Ethics Committee meet each week to monitor the progress throughout the whole trial period, which will be independent from the investigators and the sponsor.

##### Data statistical analysis

The SPSS 26.0 statistical software will be used for analysis by three-party statisticians. Data presentation: each measurement is presented as mean ± standard deviation if it conforms to a normal distribution, or median and quartiles if it does not. Intra-group comparisons: if the measurement data in each group conforms to a normal distribution, paired *T* test will be used for comparison between each group before and after treatment; if all data does not conform to a normal distribution, paired sample Wilcoxon rank sum test is used. Inter-group comparison: If the measurement data of conforms to a normal distribution, one-way ANOVA will be performed, and the LSD method will be used for comparison between the groups (Welch’s test will be used to correct Dunnett’s T3 method when the variance is not equal); if the data does not all conform to a normal distribution, non-parametric test will be performed (Mann–Whitney *U* method is applied for comparison between two groups, and Kruskal–Wallis *H* method is for comparison between multiple groups).

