**Inclusion criteria for patients**	
a. Meet the diagnostic criteria of stroke [15, 16]	a. Severe cognitive dysfunction, severe aphasia, cannot cooperate with the whole treatment or testing process
b. Age: 35 ~ 75 years old, male and female	b. Patients with serious primary diseases such as heart, lung, kidney, liver, and endocrine system
c. Course of disease: 2 weeks to 3 months after stroke, stable vital signs, basically normal cognitive function, can cooperate to complete the test	c. Neurological or musculoskeletal diseases affecting functional recovery before onset
d. Manual muscle test (MMT) ≥ 2 [17], modified Ashworth (MAS) [18] of paralyzed upper limbs are graded I ~ II	d. Cerebral stem stroke or bilateral stroke
e. Body mass index (BMI) ≤ 28	e. Patients with severe anxiety, depression, affective disorders, schizophrenia, and other serious mental disorders
f. No serious heart, lung, kidney, and other functional damage; serious underlying diseases; pain in the affected side of the upper limb joint	f. Examination confirmed by brain tumor, brain trauma, brain parasitic diseases, metabolic disorders, rheumatic heart disease, coronary heart disease, and other heart diseases with atrial fibrillation caused by cerebral embolism
g. The informed consent is signed by the patient and/or his/her family members. Note: patients who meet the above 7 criteria can be included in this study	g. Patients with skin damage, infection, or deformity at the treatment site

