##### Patients

Before and after the first and last treatment, the immediate alpha, beta, delta, and theta bands of the eyes-closed resting state EEG of patients in the two groups and ask the patients to do the “reaching and retrieving” gross motion, recording the real-time sEMG data of RMS (root mean square) and MF (median frequency). Data of the following are collected: biceps brachii (BB), triceps brachii (TB), extensor carpi radialis (ECR), brachioradialis (B), extensor digitorum (ED), and flexor carpi ulnaris (FCU) during the whole process of the motion. Computer software calculates iEMG (integrated
electromyogram) and MPF (mean power frequency) values.

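### The PES–CES comparison is planned without baseline adjustment and without naming the compared quantity, although every patient outcome has a baseline; this costs precision

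*Protocol article*

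**What the plan says.** The Data statistical analysis section of the protocol article assigns a test to each kind of comparison.

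- **Within an arm:** a paired "test will be used for comparison between each group before and after treatment", replaced by Wilcoxon if the data are not normal.
- **Between groups:** "one-way ANOVA will be performed, and the LSD method will be used for comparison between the groups", with Welch and Dunnett's T3 if variances differ. For non-normal data the Mann–Whitney U "method is applied for comparison between two groups", with Kruskal–Wallis for more than two.

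No covariate, change score or group-by-time term is named for the between-group comparison, and no time point is given for the values that enter it.

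Baselines exist throughout. EEG and sEMG are recorded in patients "Before and after the first and last treatment". The scales are covered by "Before and after the whole trial, the secondary outcome variables including MBI" and the four others, and Table 3 marks all of these outcomes at day 0.

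Two other places bear on which quantity is compared. The sample size rests on biceps RMS, for which the difference "was obtained from the pretest of group 1 and group 2 after treatment and the healthy group". Healthy controls are measured once, "Before the beginning of the whole clinical trial", so they have no change score.

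**The concern.** The question of the trial is whether PES does better than CES. As written, the only tests that use the baseline are run separately in each arm and do not compare the arms. The only tests that compare the arms do not use the baseline.

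First, precision is at stake. sEMG amplitude and motor scores can be expected to vary between patients for reasons that precede treatment. Table 1 admits "Course of disease: 2 weeks to 3 months after stroke", a span over which starting levels may differ a good deal. A baseline value that predicts the outcome removes part of this variation from the arm comparison, and with 25 to 30 patients per arm that matters.

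Second, interpretation is at stake. All patients receive conventional medication, rehabilitation and acupuncture, and CES is itself electrical stimulation at the same acupoints. The Discussion calls the first six months after stroke the favourable period for rehabilitation. Improvement in both arms is therefore to be expected, and a significant paired test in either arm does not separate PES from CES.

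**Working it through.** **Inputs from Sample size estimation.** Differences from the healthy group 167.61 and 68.17; SDs 127.22 and 148.46, taken as those of the two treated groups; effect size 0.8; α = 0.05 (two-sided assumed, sidedness not stated); power 0.80; 25 per group, 60 in total after the 20% increase.

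**Assumed.** The correlation ρ between baseline and post-treatment value is not in the document; 0.3, 0.5 and 0.7 are used. Baseline and post-treatment SDs are taken as equal.

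**1. The plan's own figure.** Normal approximation for two means: n = 2(1.96 + 0.84)²/0.8² = 24.5, so 25 per group and 50 in total; 50 × 1.2 = 60. The stated figure reproduces (the t-based version gives 25.5, so 26). It is an unadjusted comparison of one value per patient.

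**2. Effect size from the pilot figures.** Difference 167.61 − 68.17 = 99.44. Pooled SD = √[(127.22² + 148.46²)/2] = 138.25. d = 99.44/138.25 = 0.719.

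**3. Power with and without the baseline.** ANCOVA multiplies the SD by √(1 − ρ²), so the effective d is 0.719/√(1 − ρ²). Two-sided power from the noncentral t distribution:

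| Analysis | Effective d | 25 per arm | 30 per arm |
|---|---|---|---|
| Unadjusted | 0.719 | 70% | 78% |
| ANCOVA, ρ = 0.3 | 0.754 | 74% | 82% |
| ANCOVA, ρ = 0.5 | 0.831 | 82% | 89% |
| ANCOVA, ρ = 0.7 | 1.007 | 94% | 97% |

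The required sample size falls by the factor 1 − ρ²: by 9%, 25% and 51%. At the stated effect size of 0.8 that means 23, 19 and 13 per group instead of 25 (normal approximation).

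**4. If change scores were meant.** Their SD is the raw SD times √[2(1 − ρ)], a factor of 1.18, 1.00 and 0.77. The same calculation at effect size 0.8 gives 35, 25 and 15 per group. Change scores beat raw values only if ρ exceeds 0.5, and they need more patients than ANCOVA at each of these correlations.

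**5. Chance imbalance at baseline.** With 25 per arm the SD of the chance baseline difference is √(2/25) × 138.25 = 39.1 RMS units, taking the baseline SD as equal to the pooled pilot SD. Only the fraction ρ of an imbalance is expected to carry into the post-treatment difference: 0.3, 0.5 and 0.7 × 39.1 = about 12, 20 and 27 units, or 12%, 20% and 28% of 99.44.

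**The case against.** The strongest reply is that the article does not say what is compared. Its between-group tests could be applied to change scores, in which case the baseline would enter. A reader might infer that only post-treatment values are used and that the baseline is ignored. The text does not state this. The sample size basis and the single measurement of healthy controls point to post-treatment values without settling the PES–CES comparison, and the baseline is used in the paired tests. What stands is narrower: the compared quantity is undefined and no adjustment is named. Step 4 shows that ANCOVA is preferable under either reading.

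A reader might also infer that efficacy will be declared if one arm is significant and the other is not. If the arms did not differ and each paired test had power p, that rule would err with probability 2p(1 − p): 50% at p = 0.5, 32% at p = 0.8. The protocol does not adopt this rule; it plans a direct between-group comparison beside the paired tests. These figures are therefore not error rates of the plan.

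Nor does baseline imbalance pass in full into the estimate. The 39 units in step 5 would do so only at ρ = 1, or in an analysis of change scores at ρ = 0.

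The 70% is also a cautious case. At d = 0.8, unadjusted power is 79% with 25 per arm and 86% with 30. The gap between 0.72 and 0.8 is a separate sample-size question and is not counted here.

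Finally, this is a condensed article, and covariates are often left to the analysis plan. That does not remove the point, because the article does name the between-group tests, and they are unadjusted.

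**Conclusion.** The point holds as one of efficiency and clarity. It is not one of bias: randomisation keeps the unadjusted comparison unbiased. At the pilot d of 0.72 the price is about 4, 12 or 23 percentage points of power with 25 per arm (74 − 70, 82 − 70, 94 − 70, taken before rounding), and about 4, 10 or 19 with 30, at ρ of 0.3, 0.5 and 0.7. All of this rests on the assumed ρ, on equal SDs, on the pilot SDs being those of the treated groups, and on the comparison being of post-treatment values. If ρ is low, little is lost. Independently of these figures, the within-arm p-values do not bear on PES versus CES, and the text should not leave them as inferential tests on a par with the arm comparison. The change should be made, but the point does not invalidate the trial.

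**What to change.** In Data statistical analysis, make the primary comparison the PES–CES difference with its 95% CI from an ANCOVA of the post-treatment value on arm and baseline value, fitted in the patients only. State which recordings serve as baseline and as post-treatment value, since EEG and sEMG are taken several times. Healthy controls remain a descriptive reference.

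Use baseline-adjusted analyses for the secondary scales as well, with a rank-based or ordinal version for graded scales such as MMT and Brunnstrom. Report within-arm changes descriptively, and say that they are not evidence of efficacy.

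The cost is analysis wording. The baselines are already scheduled in Table 3, no patient or visit is added, and ANCOVA is available in the SPSS version named. The change should be fixed and dated before the outcome data are unblinded.

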### Study design

This clinical trial is designed as a double-blind RCT with 90 participants (60 stroke patients and 30 healthy controls) to be recruited. SPIRIT checklist and CONSORT statement were used when writing this study protocol [13, 14]. The whole study duration is about 17 weeks, including the washout period (7 days), the screening observation (3–7 days), the treatment period (3 weeks), and the follow-up period (3 months) (Fig. 1). After signing the informed consent (version date: 2021.11.19, version number: V1.1), all patients will be randomized divided into two groups in a blind manner—programmed flexor–extensor alternating electrical acupoint stimulation group (PES group) and conventional flexor–extensor alternating electrical acupoint stimulation group (CES group) with 30 cases in each, and the treatment will last for 3 weeks (6 days of treatment with 1-day rest per week). Healthy controls are used as a baseline without treatment. Participation in the trial is entirely voluntary, and they can withdraw at any time during the study without any reason. The participants are blinded, and the signal acquisition, evaluation, and outcome assessors are blinded. Because the treatment operation is too programmed, it is difficult to blind the performers. To prevent unblinding, subjects are advised not to discuss treatment options with evaluators (Figs. 2 and 3). All the patients will be followed up for 3 months. The follow-up time points will be at the end of the 1st month and 3rd month after the trial. The data and results will be monitored by the Data and Safety Monitoring Committee (DSMC) and the Ethics Committee.

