### Healthy control group

No treatment, as the baseline. Ask them to do the “reaching and retrieving” gross motion and record the resting state EEG and motion state sEMG parameters.

All the patients will receive free medical care during the study period, including counseling, therapy, electrophysiology, and scale evaluation. Participation in the trial is entirely voluntary, and patients can withdraw at any time during the study without any reason. The patient’s medical records will be kept in the hospital and only available to researchers, research authorities and ethics committee members of the Second Affiliated Hospital of Heilongjiang University of Chinese Medicine for review. Any public reporting of the results will not disclose the patients’ and healthy controls’ privacy. If the participant withdraws, their data will also be recorded but will not be used in this study.

Furthermore, for improving the adherence, the relevant staff will adequately explain the treatment method, duration, potential risks, and other details to the participants and keep connected whenever they need any medical service.

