### Measurement

*Patient demographics*: age, gender, BMI, course of disease, functional damage and serious underlying diseases, and date of admission.

*Healthy control demographics*: age, gender, BMI, once eyes-closed resting state EEG signals, and real-time sEMG signals.

*Treatment information*: enrollment time, treatment time, hospital discharge time, withdrawal time, problems in the treatment period, scale evaluation (MBI, CSS, FMA-U, MMT, and Brunnstrom), eyes-closed resting state EEG signals, and real-time sEMG signals [19].

*Follow-up*: dates of follow-up visit, adjuvant therapies, overall health status at and during follow-up (recovery condition of the upper limb, activity of daily living, fundamental diseases, drugs, death, loss of follow-up), and scale evaluation (MBI, CSS, FMA-U, MMT, and Brunnstrom). The follow-up staff will also be blinded.

The trial time enrollment schedule is estimated to be 6–8 months with a 3-month follow-up after the end of treatment. In 48 h after signing the informed consent, the patients will be randomly divided into groups according to the order in the clinic and then receive treatment after being evaluated (Table 3).

**Table 3 Tab3:** Schedule of study procedures

**Study period**	**Washout**	**Observation**	**Baseline**	**Treatment**			**Follow-up**	
Timepoint	≦7 days	3-7 days	0 day	1 day*	3 week◈	3 week^⊙^	1 month	3 month

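### The main month-1 and month-3 comparisons of MBI, CSS and FMA-U rest on single-time-point tests that use neither baseline nor the earlier scores of patients lost later, which costs precision and can cause bias

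*Protocol article*

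**What the plan says.** Table 3 of the protocol article schedules MBI, CSS, FMA-U, MMT and Brunnstrom at baseline, at the end of week 3, and at months 1 and 3. The Study design section confirms the last two: "The follow-up time points will be at the end of the 1st month and 3rd month after the trial". The Measurement section lists the same instruments for follow-up: "scale evaluation (MBI, CSS, FMA-U, MMT, and Brunnstrom). The follow-up staff will also be blinded".

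The Data statistical analysis section names the methods. Within an arm, a paired t test or its rank counterpart "will be used for comparison between each group before and after treatment". Between arms, with normal data, "one-way ANOVA will be performed, and the LSD method will be used for comparison between the groups" (with a Welch and Dunnett T3 variant for unequal variances). With non-normal data, "Mann–Whitney *U* method is applied for comparison between two groups", and Kruskal–Wallis for several groups.

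Three other statements bear on missing visits:
- Sample size estimation: "Considering the possibility of sample loss in the trial, the sample size should be increased by 20" per cent.
- Management and safety monitoring: "multiple imputation will be used to deal with the missing data as part of the sensitivity analysis".
- Interventions, under Healthy control group: "If the participant withdraws, their data will also be recorded but will not be used in this study".

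**The concern.** Each patient can contribute up to four scores per scale, but every between-arm test named takes one score per patient. Applied at month 3, such a test can use only patients who have a month-3 score, and it ignores what is already known about them from baseline, week 3 and month 1. A patient seen at week 3 and month 1 and then lost adds nothing to the main month-3 result.

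The protocol expects loss, and the patients are inpatients who must be followed for three months after a three-week course. Months 1 and 3 alone show whether a difference between programmed (PES) and conventional (CES) stimulation in motor function and daily living lasts. At stake are the precision of that answer and its protection against loss that is related to recovery.

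**Working it through.** **The plan's own figures.** With effect size 0.8, two-sided α 0.05 (sidedness assumed) and power 0.80, n = 2 × (1.96 + 0.84)² / 0.8² = 24.5, so 25 per arm and 50 in total. Then 50 × 1.2 = 60, which tolerates 10/60 = 16.7% loss. These figures reproduce, but they concern biceps RMS after treatment. They do not forecast month-3 loss on the scales.

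**Assumed inputs.** The documents give no scale SD, no between-visit correlation and no follow-up loss rate. Assumed: outcome SD 1, 30 per arm, about 10% lost before month 1 and 20% by month 3 (24 per arm left), baseline correlation 0.5 to 0.7, adjacent post-treatment correlation 0.75 to 0.90, true effect 0.5 SD.

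**Precision under random loss.**
- Single-visit test: √(2/24) = 0.289.
- With baseline adjustment: 0.289 × √(1 − 0.5²) = 0.250, and 0.289 × √(1 − 0.7²) = 0.206.
- Simulation agrees: 0.29 for the single-visit test, 0.21 to 0.25 for ANCOVA on attendees, 0.20 to 0.24 for the repeated-measures estimate.
- A second set of runs gave 0.293 / 0.235 / 0.218 (adjacent correlation 0.90) and 0.294 / 0.257 / 0.248 (0.75). The gain from linking visits alone is therefore 1 − 0.218/0.235 = 7% and 1 − 0.248/0.257 = 4%.

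**Cross-check without baseline.** If a share f is lost at random and an earlier score correlates r with month 3, the single-visit variance exceeds that of the linked estimate by the factor 1/(1 − f r²). With f = 0.19 this is 1.05, 1.10 and 1.16 for r = 0.5, 0.7 and 0.85. Simulation gave 1.05, 1.11 and 1.17.

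**Bias when loss depends on earlier scores (true effect 0.50).**

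| Loss pattern | Single-visit test | ANCOVA, attendees | Repeated measures |
|---|---|---|---|
| Poor scorers leave, CES only (first runs) | 0.31–0.35 | 0.40–0.42 | 0.49–0.50 |
| Same pattern (second runs) | 0.34–0.37 | 0.41–0.42 | 0.50 |
| One score rule in both arms | 0.43–0.44 | 0.46–0.47 | 0.50 |

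The single-visit shortfall is 0.13 to 0.19 when dependence is in CES only (0.50 − 0.37 to 0.50 − 0.31) and 0.06 to 0.07 under a common rule. Baseline adjustment alone leaves 0.08 to 0.10 and 0.03 to 0.04.

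**A further simulation** (true effect 0.8 SD, correlation 0.5 to 0.85, no baseline, 4,000 trials per setting) gave these single-visit biases:
- Same dependence relative to each arm's own mean: at most 0.01.
- Dependence in PES only, poor scorers leaving: +0.11 to +0.19.
- Opposite dependence in the two arms: +0.22 to +0.37.
- One rule on the actual score: −0.04 to −0.07, or −0.11 to −0.19 with a rule twice as steep that loses about 17% of one arm and 36% of the other.

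The linked estimate was within about 0.005 of the truth throughout.

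**The case against.** The strongest reply is that the analysis section never mentions months 1 and 3 and states no analysis set, and that modelling detail may sit in a full plan that is not shown. A reader might infer that the protocol commits to analysing attendees only. It does not say so; that follows from the tests named. But the protocol does choose its between-arm methods, its fallback rules and its software, and none of those methods can carry a patient's earlier scores. The point concerns a stated method, not absent detail.

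A reader might also infer that earlier scores are never used. Multiple imputation could bring them in, under much the same assumption as a mixed model. Its variables are not given, and it is assigned to the sensitivity analysis, so the main result stays as described.

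Nor do the documents support saying that recovery-related loss always biases the comparison. It does not when the dependence is equal around each arm's mean, and nothing in the documents says which pattern to expect. The sign reverses if the pattern reverses.

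The gain from linking visits is modest and not universal. Under score-dependent loss without baseline, the single-visit variance ranged from 2% smaller to 14% larger when loss was spread over both follow-up visits. Under one rule on the actual score, the single-visit SD was equal or smaller in most runs.

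Finally, these are secondary outcomes. The sEMG and EEG measures end at week 3, so neither the primary result nor the sample size is at risk from follow-up loss.

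**Conclusion.** The point holds in a limited form. For MBI, CSS and FMA-U, the main follow-up comparisons are less precise than the planned data allow: an SD of about 0.29 against about 0.20 to 0.24, most of it from unused baseline and about 4 to 7% from unlinked visits. They are also open to bias, from near zero to about 0.13 to 0.19 SD when dependence is in one arm only, and more in the extreme patterns shown.

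All sizes rest on assumed correlations, loss rates and normal scores. The mixed model's protection holds when loss depends on scores already recorded; it does not extend to loss driven by the unseen month-3 outcome. This is a worthwhile improvement to the secondary analysis and not a threat to the trial's primary result.

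**What to change.** In the Data statistical analysis section, make the main between-arm analysis of MBI, CSS and FMA-U one linear mixed model for repeated measures (MIXED in the planned SPSS 26.0):
- Outcomes: week-3, month-1 and month-3 scores.
- Fixed effects: arm, visit, arm-by-visit, baseline score and baseline-by-visit, with unstructured covariance.
- Population: every randomised patient with at least one post-baseline score.
- Report: PES minus CES with 95% CI at each visit.

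Keep rank or ordinal methods for MMT and Brunnstrom. Keep multiple imputation and the non-parametric test as sensitivity analyses.

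The model cannot do its full work while withdrawn participants' data are set aside. Amend that sentence so that data collected before withdrawal are used as far as consent allows.

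The cost is one paragraph of analysis text and one amended sentence, checked against the consent wording. No new visits, patients or software are needed. The small downside is that the model assumes roughly normal residuals on bounded scales and estimates a few more covariance parameters.
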